# Effects of a self-care educational program via telerehabilitation on quality of life and caregiver burden in amyotrophic lateral sclerosis: a single-blinded randomized clinical trial protocol

**DOI:** 10.3389/fpsyg.2023.1164370

**Published:** 2023-08-17

**Keywords:** caregivers, amyotrophic lateral sclerosis, telerehabilitation, self-care education, burden, quality of life

## Abstract

**Introduction:**

The implementation of a telerehabilitation protocol for self-care in the routine of caregivers of individuals with amyotrophic lateral sclerosis (ALS) has been associated with reduced levels of stress and improved quality of life. Moreover, it may reduce the difficulty of traveling to perform physical or other self-care activities. Thus, this study designed a clinical trial protocol to investigate the effects of a self-care education program via telerehabilitation on the burden and quality of life of caregivers of individuals with ALS.

**Methods:**

This single-blinded randomized clinical trial will recruit 26 caregivers and randomly allocate them to the experimental (EG = 13) or control group (CG = 13). The EG will receive an informative booklet and participate in a 6-week synchronous telerehabilitation program with a neuropsychologist, nutritionist, and physiotherapist to discuss physical and mental health. The CG will receive an informative booklet on self-care and physical activity and weekly phone calls for 6 weeks to solve questions about the booklet. Outcomes will include the caregiver burden (Zarit scale), quality of life (World Health Organization Quality of Life BREF), pain (McGill Pain Questionnaire), stress (Perceived Stress Scale), and depression (Beck Depression Inventory), which will be evaluated at the baseline after the six-week program and 30 days after the program. Additionally, we will assess daily the nocturnal awakenings, sleep patterns, level of physical activity, and heart rate variability.

**Discussion:**

This study aimed to investigate the effectiveness of telerehabilitation for caregivers of individuals with ALS. If effective, this program could be disseminated among health professionals, increasing the possibility of remotely monitoring individuals with difficulty performing physical activities.

**Trial registration number:**

NCT05884034 (clinicaltrials.gov).

## 1. Introduction

Caregivers have a low quality of life due to the patient worsening, challenges faced with the progression of the health condition, changes in the routine, and reduction in leisure activities (Diniz et al., 2018; Alves et al., 2019; Nogueira et al., 2019; Sanches Slusarski Martins et al., 2022). Although the low quality of life and increased burden of caregivers are well-established characteristics in literature, this topic still requires greater visibility and attention to propose interventions (Burke et al., 2017; Sandstedt et al., 2018).

Informal caregivers (i.e., unpaid individuals who help patients in activities of daily living and medical programming) may also experience issues in family relationships and economic difficulties and suffer from social stigma and physical burden (Ploeg et al., 2017). Approximately 70 to 80% of caregivers are informal; among these, 30 to 68% have anxiety or depression (Wilz and Kalytta, 2008). In addition, the strain increases the risk of cardiovascular diseases and mortality by 23 and 63%, respectively (Richard and Scott, 1999).

Individuals with amyotrophic lateral sclerosis (ALS) present progressive muscle weakness, fatigue, and reduced mobility and functional activities (Lui and Byl, 2009). Moreover, a multidisciplinary team treats ALS focusing on symptoms (Ferreira et al., 2016) since this disease progression cannot be reversed or changed, requiring intermittent care. Informal caregivers are essential to support this population due to the intensive and complex care required (D'Alvano et al., 2022; Poppe et al., 2022). Schischlevskij et al. (2021) found that the functional status and disease severity of individuals with ALS were the main factors influencing caregiver burden. Moreover, cognitive changes (e.g., impaired attention, focus, and memory) and behavioral changes (e.g., irritability, frustration, impatience, and social isolation) in caregivers of individuals with ALS (Burke et al., 2015; Beeldman et al., 2016) and the need to learn how to manage assisted ventilation and enteral feeding has been involved in caregiver burden (Siciliano et al., 2017; Chu and Oh, 2020).

Weight loss in ALS has been associated with reduced survival; thus, healthcare professionals must establish maintaining body weight as a therapeutic goal (Ning et al., 2019; van Mantgem et al., 2020). In this sense, caregivers' knowledge and influence on nutritional behaviors are essential to increase caloric intake and body weight in individuals with ALS (Genton et al., 2011; Marin et al., 2011; Coates et al., 2023). Thus, a support network should be implemented to help with nutritional issues in this disease (Ludolph et al., 2020).

The implementation of physical activity in the routine of caregivers has been associated with reduced stress and improved quality of life and wellbeing (Lambert et al., 2016). However, caregiving demands hamper the adherence to face-to-face programs due to the limited time available, the need for travel, and difficulty finding someone to care for the patient (Winter and Gitlin, 2007). Thus, remote self-care activities are faster and more practical than face-to-face and may be preferred (Hearn et al., 2019) since caregivers can participate in meetings and receive professional guidance and information via video conferences (Van Egmond et al., 2018).

The self-care concept comprises actions to ensure self-health and wellbeing (Lobo et al., 2023). In this sense, caregivers of individuals with ALS need to recognize the importance of self-care since they face great physical and emotional challenges (Young et al., 2023). Moreover, caregivers can maintain their health and quality of life by prioritizing self-care, which improves their ability to care for the patient adequately and efficiently (D'Alvano et al., 2022).

Telerehabilitation is defined as remote rehabilitation via communication technologies that different health professionals can use (e.g., physical, occupational, and speech therapists and psychologists). This tool can be combined with evaluation, monitoring, and health education, may reduce travel costs, and allow flexible schedules and integration into the routine of users (Van Egmond et al., 2018). Moreover, telerehabilitation can be implemented asynchronously (i.e., without real-time contact) or synchronously (i.e., real-time video and audio) using video conferences with one or more individuals simultaneously (Kern, 2006).

Previous studies (Cottrell et al., 2017; Grona et al., 2018; Jiang et al., 2018; Bettger et al., 2020; Prvu Bettger and Resnik, 2020; Yeroushalmi et al., 2020) have shown that telerehabilitation may reduce pain and recover motor function in individuals with musculoskeletal dysfunctions. Moreover, it decreases healthcare costs and improves treatment adherence, physical and mental function, and quality of life (Barlow et al., 2009; Vloothuis et al., 2019).

Educational programs can provide information to cope with the challenges of caregiving and implement relevant topics based on self-care (e.g., sleep health, healthy eating, mental health practices, and physical exercises to support the caregivers' quality of life), allowing informal caregivers to have confidence in providing care and focus on their physical and mental wellbeing (González-Fraile et al., 2021; Zarotti et al., 2021). However, the effects of telerehabilitation on informal caregivers of individuals with ALS are unclear (Watermeyer et al., 2015; Galvin et al., 2018; Burke et al., 2019) since the needs and circumstances may vary for each caregiver and the patient and due to different training programs and telerehabilitation limitations. Moreover, a lack of studies regarding the long-term effects of continuous remote evaluation and telerehabilitation and its efficacy in different disease stages has been observed, hampering to generalize of the studied effects.

In this sense, the following question emerged: Does the quality of life, depression, burden, and stress of caregivers receiving a synchronous telerehabilitation program improve compared with those assisted individually and asynchronously? Thus, we hypothesized that a synchronous telerehabilitation program might reduce the burden, stress, pain, and depression and improve the quality of life of caregivers of individuals with ALS, enhancing their mental and physical health. The benefits may include reduced social isolation and improved access to support and guidance services, coping strategies for stress and emotional burden, and knowledge regarding ALS and adequate care strategies.

This study aimed to design a randomized clinical trial protocol to evaluate the impact of a self-care education program via synchronous telerehabilitation on the quality of life and burden of caregivers of individuals with ALS. All the content addressed in both intervention proposals is innovative, as planned by a multidisciplinary team, aiming to consider different aspects that influence the quality of life, depression, burden, pain, and stress of caregivers. Additionally, the present study will use wearable technologies as a way to monitor and assess physiological states remotely, such as nocturnal awakenings, sleep patterns, level of physical activity, and heart rate variability. Results may show whether remote and synchronous programs favor the self-care of caregivers by improving time and access to health education.

## 2. Methods

### 2.1. Study design

This protocol for a single-blinded randomized clinical trial was developed according to the Standard Protocol Items: Recommendations for Interventional Trials (SPIRIT) (Chan et al., 2013) (see SPIRIT checklist in Supplementary material 1).

### 2.2. Target population and sampling

Participants will comprise informal caregivers of individuals with ALS of both sexes diagnosed by a neurologist (El Escorial criteria) (Brooks et al., 2000), aged 18 years or above, and living in the municipalities of Natal (Rio Grande do Norte, Brazil). They will be recruited using the attendance and waiting list from the Neuromuscular Diseases Outpatient Clinic of the Onofre Lopes University Hospital–HUOL/UFRN/EBSERH. Thus, all participants will be initially contacted through their phone number provided during the registration in these lists.

### 2.3. Power calculation

Sample size was estimated using an online calculator (Dean, 2007) based on caregiver burden (primary outcome), which was evaluated using the Zarit scale. Moreover, the effect size was calculated based on post-training data from Duran Parra et al. (2019) (mean of 16 ± 9.9 and 31.4 ± 14.9 points for experimental and control groups, respectively), with a mean difference of 15.4 between groups. Thus, 22 participants (11 per group) were estimated, and the total sample was determined as 26 participants (13 per group), considering a dropout rate of 20%.

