### 2.14. Statistical analysis

Data will be analyzed using the Statistical Package for the Social Sciences software version 22.0 (IBM Corp., Chicago, IL, USA). Data will be initially characterized using descriptive analysis, and the significance level will be set at 5%. The Shapiro-Wilk test will be applied to verify data normality. Differences between groups on different evaluation periods will be analyzed using linear mixed models. The Bonferroni *post hoc* may be used for statistically significant results to identify specific differences. Moreover, an intention-to-treat analysis will be used to compare the groups by including all participants as allocated after randomization, ensuring an unbiased approach. Participants' data will be analyzed based on their intervention group, regardless of any dropouts. Values from the previous evaluation will be replicated and attributed to missing data due to dropout.

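### Randomising 26 covers about 15% dropout, not the 20% that section 2.3 claims (minor)

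*Protocol article*

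**What the plan says.** Protocol article, section 2.3 (Power calculation), bases the sample size on caregiver burden measured by the Zarit scale. It uses post-training figures from one earlier study: "mean of 16 ± 9.9 and 31.4 ± 14.9 points for experimental and control groups", "with a mean difference of 15.4 between groups". From these, "22 participants (11 per group) were estimated". The section then moves to the number to enrol: "the total sample was determined as 26 participants (13 per group), considering a dropout rate of 20" per cent. No inflation formula is shown.

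The Abstract (Methods) repeats the total: the trial "will recruit 26 caregivers and randomly allocate them to the experimental (EG = 13) or control group (CG = 13").

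Section 2.14 says that "the significance level will be set at 5" per cent. It plans linear mixed models and an intention-to-treat analysis in which a dropout's missing value is filled with the value from the preceding evaluation. Neither section gives the target power or says whether the test is one- or two-sided.

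**The concern.** A dropout allowance exists so that the number the calculation calls for is still there after the expected loss. Section 2.3 names the number needed, the expected loss and the number to enrol, so a reader can check the third against the first two. A dropout rate is a share of those enrolled, so the remainder is the enrolled number times (1 − rate). On that check, 26 falls short of 22.

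What is at stake is modest. The total of 26 is the size the trial relies on, and the text tells readers that it withstands a 20% loss when it does not. If 20% do drop out, the trial will have fewer completers than it planned for, and section 2.3 gives no warning of this.

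**Working it through.** **Inputs.** All from section 2.3 unless noted: needed 22 (11 per group); dropout 20%; enrolled 26 (13 per group); means 16 and 31.4; SDs 9.9 and 14.9; difference 15.4. Significance level 5% from section 2.14. Assumed, because not stated: two-sided test and 80% target power. The dropout check in steps 2 to 4 uses neither assumption.

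**1. Reproduce the base size.** Normal approximation for two means:

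n per group = (SD₁² + SD₂²) × (1.960 + 0.842)² / difference²
= (98.01 + 222.01) × 7.849 / 237.16
= 320.02 × 7.849 / 237.16 = 10.59, rounded up to 11.

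This gives 22 in total and matches the plan. With the same formula, 85% power gives 13 per group and 90% gives 15, so 80% is the natural reading.

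**2. What 26 leaves after a 20% loss.**
- Total: 26 × 0.8 = 20.8, against 22 needed.
- Per group: 13 × 0.8 = 10.4, against 11 needed.
- Largest loss that still leaves 22: 1 − 22/26 = 4/26 = 15.4%.

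**3. What a 20% allowance requires.**
- Total: 22 / 0.8 = 27.5, rounded up to 28.
- Per group: 11 / 0.8 = 13.75, rounded up to 14.
- Check: 28 × 0.8 = 22.4, which is at least 22.

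**4. Likely origin of 26.** 22 × 1.2 = 26.4 (11 × 1.2 = 13.2 per group), rounded down to 26 (13 per group). This is an inference, since the article does not show the step.

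**5. Size of the effect on power.** Difference 15.4, SDs as above, two-sided 5%:

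| Completers per group | Normal approximation | Two-sample t-test |
|---|---|---|
| 11 (as estimated) | 81.5% | 77.5% |
| 10.4 (26 less 20%) | 79.3% | 74.9% |
| Loss | 2.2 points | 2.6 points |

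The normal figures come from Φ(15.4 / √(320.02/n) − 1.960). At n = 11 this is Φ(2.855 − 1.960) = Φ(0.895). At n = 10.4 it is Φ(2.776 − 1.960) = Φ(0.816). The t-test figures use the noncentral t distribution with 2n − 2 degrees of freedom.

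**The case against.** **The 20% may mean 20% added to the number needed.** That would explain the multiplication, but the text calls it a dropout rate. Even as an added margin, 26.4 rounds up to 27 in total, and 13.2 rounds up to 14 per group, so 26 is short on that reading too. The wording or the number needs correcting either way.

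**Intention-to-treat with carried-forward values keeps all 26 in the analysis.** This is true of the nominal number analysed under section 2.14, and section 2.3 does not itself call the 22 completers. But a repeated earlier value adds no new post-programme information. If carrying forward were thought to make up for dropout, there would have been no reason to enlarge 22 at all. This objection softens the consequence without removing the inconsistency.

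**The gap is trivial.** It is about 1.2 completers, or two enrolled participants, and 2 to 3 points of power. That is small beside the uncertainty in a standardised difference of about 1.22 (15.4 / 12.65) taken from one earlier study. This stands, and it sets the severity.

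**A stronger reading that does not hold.** A reader might infer that the base size is also wrong, because a t-based calculation on the same figures needs 12 per group (81.3% power, against 77.5% at 11), or that the trial would have only about 73% power. The documents do not support either. The section says "Sample size was estimated using an online calculator", and 11 per group follows exactly from a standard formula, so choosing the t-based one is a preference and not a correction. No target power is stated for the design to miss. The 73% figure requires 10 per group, a loss of 6 of 26 (23%), not 20%. Most of the gap between the t-test figures and 80% is already there at 11 per group and has nothing to do with dropout. The planned analysis is a linear mixed model, so simple two-group power figures serve only to size the change.

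**Conclusion.** The inconsistency is real and follows from section 2.3's own figures: 26 enrolled covers a 15.4% loss, while a 20% loss leaves 20.8, about one short of the 22 estimated. The arithmetic rests on no assumption beyond reading the dropout rate as a share of those enrolled.

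The consequence is small. Power falls from about 81.5% to 79.3% on the normal approximation, or from about 77.5% to 74.9% on a t-test, with two-sided 5% assumed in both. The estimate of 11 per group is sound on the formula that reproduces it. Severity is minor: a stated figure to be corrected, with no threat to the design.

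**What to change.** Restate the end of section 2.3 along these lines: *26 randomised allows for about 15% dropout (4 of 26); at 20% dropout about 21 would remain, slightly below the 22 estimated.* This costs nothing beyond a slightly less favourable sentence, and the total in the Abstract can stay as it is.

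If 20% is to be covered, the consistent total is 28 (14 per group), and both section 2.3 and the Abstract need the new figure. The cost is two more participants. Neither option changes the design, the outcomes or the planned analysis.

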### 2.4. Consent for publication and confidentiality

Information of all participants will be confidential and maintained in a safe place in the laboratory for at least 5 years. Only the corresponding author will access these data, ensuring anonymity, respect, and human dignity. Moreover, the information will only be disclosed anonymously, without initials or indications that could identify the participants.

The findings will be published in peer-reviewed journals and presented at conferences. In case of significant changes in the protocol, we will inform the participants, ClinicalTrials.gov, and journals. A copy of the informed consent form will be provided upon request.

### 2.5. Availability of protocol and data

Information on this randomized clinical trial protocol is registered and available. The corresponding author will provide the study protocol and data supporting the findings upon reasonable request.

### 2.6. Eligibility criteria

#### 2.6.1. Inclusion criteria

Informal caregiver (i.e., family member, friend, or a caregiver without payment) of an individual with ALS (clinically defined, probable, or possible) diagnosed by a neurologist using the (El Escorial Criteria) (Brooks et al., 2000);Informal caregiver of individuals without other neurological diseases associated with ALS (Brooks et al., 2000);Aged 18 years or above;Without cognitive impairment on the Mini-Mental State Examination (MMSE; cutoff point of 25 for literate individuals) to understand the study and the informed consent form Brucki et al. (2003);Literate (at least complete primary education).

#### 2.6.2. Exclusion criteria

Health conditions hindering exercise safety (e.g., recent surgeries, fractures, uncontrolled heart, vascular, or respiratory disorders, dizziness or vertigo, fainting, oncological diseases, or neurological diseases affecting balance and protective reactions)Caregivers in the first trimester of pregnancy (to avoid sudden increase in resting heart rate) (Wolfe and Davies, 2003);Using psychiatric medication (e.g., anxiolytics, antidepressants, antipsychotics, or antiepileptics) since they may interfere with the study resultsAbsence in the program for two or more consecutive days without replacement.

### 2.7. Randomization, allocation, and blinding

Participants will be randomly allocated into the experimental (EG) or control group (CG). A researcher not involved in the intervention will perform the randomization using the www.randomization.com website and maintain the sequence confidential in opaque sealed and numbered envelopes using codes to identify the groups. The content of envelopes will be revealed to the professionals applying the interventions only at the beginning of the program. The researcher responsible for data analysis will be blinded until the end of the study and will not be involved in interventions or data analysis. Professionals, with the exception of the researcher responsible for data analysis, and participants will not be blinded due to the nature of the intervention.

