### 2.8. Intervention groups

#### 2.8.1. Experimental group

A physiotherapist will visit the participants of the EG face-to-face to evaluate their health, deliver the informative booklet, and instruct its use and importance. The booklet titled “Self-care program for caregivers of individuals with ALS” contains guidelines for performing physical activities at home (e.g., stretching, mobility, and strengthening) and information on healthy eating, mental health, and routine management, with a schedule for the weekly organization (Appendix 1).

Participants in EG will be divided into subgroups (three to five per subgroup). Each subgroup will participate in a 6-week self-care education program with weekly synchronous meetings (Burke et al., 2019; de Wit et al., 2019) using Google Meet or WhatsApp. Each meeting will address topics related to the physical and mental health of caregivers, including the importance of care and caregivers, physical activities to be performed at home, routine management, and healthy eating (Figure 1). A physiotherapist, psychologist, and nutritionist will lead the meetings, which will last approximately 40 min plus a maximum of 20 min to discuss whether the participants' expectations were met.

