#### 2.8.2. Control group

A physiotherapist will also visit the participants in the CG to evaluate their health condition, deliver the informative booklet, and instruct them on the importance of reading and using the booklet (Appendix 1). Next, trained researchers will contact the participants via phone calls during the 2nd to 6th week of the intervention to verify their physical and mental health and collect information on completing physical exercises and habits proposed in the booklet. The researcher should record any relevant information. Figure 2 shows the questions for participants. After the intervention period, a new visit will be performed for revaluation.

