### 2.9. Study procedures

After receiving the informative booklet, participants will respond to questionnaires to characterize the sample and evaluate cognitive function. In the baseline evaluation, the caregiver burden, quality of life, pain, stress, and depression will be evaluated. Next, participants will be randomly assigned to the CG or EG. Outcomes will be revaluated after the 6-week program (revaluation 1) and 30 days after the program (revaluation 2) (Figure 3). If the EG shows better results than CG at the end of the study, the same intervention will be available for CG to ensure equality of treatment for all participants.

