### 2.11. Outcomes

Outcomes will be evaluated at the baseline, immediately after the 6-week program, and 30 days after the end of the program. A researcher not involved in the intervention will remotely reassess all participants via *Whatsapp* or *Google Meet*.

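### The blinding rule in 2.7 contradicts itself and no section blinds the outcome assessor; 2.8.2 and 2.11 also disagree on how revaluation is done, so assessment mode could differ by arm

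*Protocol article*

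**What the plan says.** **Blinding (protocol article, 2.7).** The sentence that grants a blind says that the "researcher responsible for data analysis will be blinded until the end of the study and will not be involved in interventions or data analysis". The next one lists who is not blinded: "Professionals, with the exception of the researcher responsible for data analysis, and participants will not be blinded", and gives the nature of the intervention as the reason.

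**Outcome assessor (2.11).** "A researcher not involved in the intervention will remotely reassess all participants", by WhatsApp or Google Meet. Nothing is said about whether this person knows the allocation.

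**Mode of revaluation.** The control-group section (2.8.2) ends: "After the intervention period, a new visit will be performed for revaluation". The experimental-group section (2.8.1) describes a first visit only: "A physiotherapist will visit the participants of the EG face-to-face to evaluate their health, deliver the informative booklet". Section 2.9 sets two revaluations for both arms, after the 6-week program and 30 days later, without naming a mode.

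**The concern.** Both primary outcomes (Zarit burden and WHOQOL-BREF quality of life) are questionnaires, as are pain, stress and depression. The participants who answer them know their arm. The protection left within the measurement process is that the questions are put in the same way in both arms by someone who does not know the allocation. The article secures neither. The only blind is given to a role described in terms that cannot all be true, and the mode of revaluation is stated in two ways, one of them only in the control-group section. If assessment mode, or the interviewer's expectation, tracked arm, its effect would be part of the estimated group difference. The linear mixed model in 2.14 could not separate the two.

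**Working it through.** The check is mainly a comparison of sections.

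**Step 1: who is blinded?**

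| Role | Stated in | Blinded? |
|---|---|---|
| Participants | 2.7 | No |
| Professionals other than the analyst | 2.7 | No |
| Researcher responsible for data analysis | 2.7 | Yes, but also said to take no part in data analysis |
| Researcher who reassesses participants | 2.11 | Not stated; only separated from the intervention |

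The third row cannot be carried out. The fourth leaves a gap, because not delivering the intervention is different from not knowing the allocation. Section 2.7 itself shows this: the researcher who generates and keeps the sequence is also described as not involved in the intervention, and that person holds the allocation list. The article does not say that these are two different people.

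**Step 2: how is revaluation done?**

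| Section | Applies to | Mode |
|---|---|---|
| 2.8.1 | Experimental group | First visit face to face; no revaluation described |
| 2.8.2 | Control group | A new visit after the intervention period |
| 2.9 | Both arms | Two time points, no mode |
| 2.11 | All participants | Remote |

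For controls, 2.8.2 and 2.11 differ. For the experimental group, only 2.11 gives a mode.

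**Step 3: what would a difference in mode do?** Let m be the mean shift in a score when it is taken in person rather than remotely, and let p be the share of an arm reassessed in person. The shift in the control-minus-experimental difference is

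m × (p in controls − p in experimental group).

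- If 2.11 governs both arms: m × (0 − 0) = 0.
- If 2.8.2 is followed for controls and 2.11 for the experimental group: m × (1 − 0) = m. Mode and arm then coincide, and no covariate adjustment can part them.

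**Step 4: scale.** The documents give no value for m. The one yardstick is the planned Zarit difference in 2.3: 31.4 − 16 = 15.4 points. Purely as an assumption, with modes fully aligned to arm:

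- m = 1: 1 / 15.4 = 6%
- m = 3: 3 / 15.4 = 19%
- m = 5: 5 / 15.4 = 32%

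These ratios only set a scale and are not evidence that such a shift exists. No planned difference is given for WHOQOL-BREF, so the same comparison cannot be made there.

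**Step 5: is the sample size affected?** No. With common SD = √((9.9² + 14.9²)/2) = 12.65 and a difference of 15.4, the normal formula at two-sided 5% and 80% power (sidedness and power are assumed, as 2.3 and 2.14 do not state them) gives 11 per group, as 2.3 says. Nothing in this point changes that.

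**The case against.** Three stronger readings are tempting, and the documents do not support them.

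- **That the assessor is unblinded by rule.** A reader might infer this because 2.7 excepts only the analyst. But the word professionals is used just before for those applying the interventions, and the reason given for not blinding is the nature of the intervention. It can fairly be read as intervention staff, which leaves the assessor out. The faulty sentence may even be a slip for the assessor, since taking no part in interventions or analysis describes an assessor well. What stands is that assessor blinding is not provided for.
- **That controls are to be seen in person and the experimental group by video.** No section plans this. Section 2.11 covers all participants, and 2.8.2 says neither who makes the new visit nor whether it is in person. The silence of 2.8.1 proves nothing, because 2.9 and 2.11 cover that arm, and the flowchart (Figure 3) is not available here. What stands is a conflict between two sections that permits the outcome.
- **That the analyst would have no data.** A reader might infer this from 2.4, where "Only the corresponding author will access these data". That is a confidentiality rule. Nothing says that the corresponding author is not the analyst, or that a coded extract is barred, so 2.4 is no part of this point.

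It can also be said that an article condenses a fuller protocol, where masking of the assessor may be described. That would fill the gap in 2.11, but it would not cure the published sentence in 2.7 or the disagreement between 2.8.2 and 2.11. Lastly, blinding an assessor does little about the expectations of participants who know their arm. That is true and limits the gain from the fix.

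**Conclusion.** The point holds as two inconsistencies and one gap. The blinding sentence in 2.7 cannot be carried out as written. No section provides for blinding the researcher who repeats the questionnaires. Sections 2.8.2 and 2.11 give different accounts of revaluation for controls. Together these leave room for measurement that depends on arm, on self-reported primary outcomes. The size of any resulting bias is unknown: it is nil if 2.11 is applied to everyone by a person who does not know the allocation, and the 6% to 32% above rests wholly on assumed shifts of 1 to 5 points with mode fully aligned to arm. The matter should be settled before the first revaluation, because measurements already taken in different modes or by an assessor aware of the arm cannot be repaired in the analysis.

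**What to change.** 1. **Section 2.7:** replace the contradictory sentence with two statements. The researcher who carries out the revaluations (already in 2.11 and not involved in the intervention) is blinded to allocation, and participants are asked not to reveal their arm. The analyst works on data with coded groups.
2. **Sections 2.8.2 and 2.11:** reconcile them so that both arms are reassessed in the same mode, by that researcher, at both revaluations.
3. **Limits:** state that participants remain unblinded, so that a reader does not take the single blind to protect the self-reports themselves.

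The cost is protocol wording and a short instruction to an assessor who is already planned. It adds no staff, visits or participants. Section 2.4 needs no change.
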